### Experimental arms

#### Control

Calling our control arm 'usual care' would be a misnomer, because it refers to usual care provided via specialized SPC and monthly visits with a study nurse. All three SPCs that will enroll patients have standardized approaches, protocols, and guidelines with respect to definitions and diagnoses of stroke and TIA; routine investigations to determine potential benefit of surgical approaches; routine application of anti-platelet medications; and routine suggestions to primary care physicians with respect to vascular risk factors such as hypertension, dyslipidemia, smoking, and other lifestyle issues. However, similar to other jurisdictions, our SPC current practice, confirmed in our pilot data [7,8] suggests that these clinics do not undertake active ongoing management of vascular risk factors but rather instead provide suggestions and directions to each patient's primary care physician. Patients randomized to the control arm will receive the same educational materials about stroke risk factors and medication adherence as the intervention patients, will be seen monthly by a study nurse, will have the same number of BP measurements, and will have a fax sent to their family physician after each study visit reporting their BP and current medications. Of note, our control arm actually represents the intervention used in our recently published SCRIP-HTN trial in individuals with diabetes which resulted in a 5 mm Hg reduction in systolic BPs compared to usual care (p = 0.03) [34]. Thus, some might consider our study to be an active-comparator trial.

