#### BP measurement

Systolic BP will be ascertained at all study visits using the BPTru^® ^device, with six readings performed one minute apart in the arm with the highest reading, and last five readings averaged. These are similar to the methods used in the Canadian health measures survey [56] and the third national health and nutrition examination survey (NHANES III). The BpTRU^® ^automated device has been approved by both the Canadian Hypertension Education Program and the Association for the Advancement of Medical Instrumentation.

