#### Outcomes

Because this is an active control trial, we expect improvements in all aspects of care in the control arm--due to both active intervention by stroke specialists within the SPCs and the referring primary care physicians in response to the monthly reminders about each study participant's BP, various secular/temporal influences as they relate to vascular risk reduction, study volunteer and Hawthorne effects, and regression to the mean. The importance of a control group cannot be over-emphasized. For example, in the ESP-CAD trial, we found a 50% absolute improvement in statin management in the control group [35]. Therefore, all continuous measurements will be 'changes' from baseline to six months, comparing the changes achieved in the intervention group with those in the control group.

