### Statistical analysis

All sociodemographic and clinical characteristics at baseline and follow-up will be summarized using percentages for categorical variables and medians (interquartile range) for continuous variables. Chi square tests will be used to compare the proportion of patients who attain 'optimal BP and lipid control' at six months (because the proportion at baseline will be zero by definition), as well as other binary secondary outcomes such as proportions that achieve target BP and lipid levels. Patient and health system factors associated with meeting BP and lipid goals will be assessed in multivariate analyses. To compare changes in systolic BP, LDL cholesterol, and total:HDL cholesterol ratios between intervention and control, we will use 2-sample independent t-tests. In the event that any baseline characteristics are not balanced between study groups, we will employ multivariate extensions of our primary analytic plan (*i.e*., substituting multiple linear regression for t-test or multiple logistic regression for Chi square test), adjusting for any clinically important (*i.e*., greater than 10% imbalance between arms) or statistically significant (*i.e*., p-value of < 0.10 between arms) differences observed between groups.

All analyses will be by intention to treat. Missing data at the six-month follow-up assessment will be imputed with a 'baseline-observation carried forward' strategy; this approach conservatively assumes that all subjects lost to follow-up have had no change in their BP or lipid levels. As a sensitivity analysis for this assumption, we will also analyze the data in an 'on-treatment' analysis, using only those cases with complete follow-up data for each analysis.

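### Baseline-observation-carried-forward is not conservative for the between-arm difference if more control patients are lost, and the stated check is a complete-case analysis, not an on-treatment one

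*Protocol article*

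**What the plan says.** The Statistical analysis section of the protocol article fixes the rule: "Missing data at the six-month follow-up assessment will be imputed with a 'baseline-observation carried forward' strategy". It gives the reason that "this approach conservatively assumes that all subjects lost to follow-up have had no change in their BP or lipid levels". It names one sensitivity analysis: "we will also analyze the data in an 'on-treatment' analysis, using only those cases with complete follow-up data for each analysis".

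Three other places bear on this:

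- Outcomes: "we expect improvements in all aspects of care in the control arm". The reasons listed include reminders to physicians, secular trends, Hawthorne effects and regression to the mean.
- Study participants and Screening: a patient may enter on systolic BP alone, on LDL alone, or on the total:HDL ratio alone.
- BP measurement and Control: "Systolic BP will be ascertained at all study visits", and control patients "will have the same number of BP measurements" as intervention patients. Interim SBP readings therefore exist in both arms.

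**The concern.** Assuming no change is pessimistic for any one patient who would have improved. The trial, however, estimates a difference between two arms that are both expected to improve. Setting a lost control patient to no change removes real control-arm improvement. If controls are lost more often, the difference moves toward the intervention, while the text tells readers that the rule errs the other way. Patients know their arm in this open-label trial, so unequal loss is possible.

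Two further effects follow. A baseline value that was already at goal is carried forward as a success on that component, although nothing was measured at six months. Filled-in zero changes also enter the t-tests as if observed, which reduces the apparent spread.

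**Working it through.** **The plan's own figures.** For 5% versus 15%, two-sided alpha 0.05 and 80% power, the pooled-variance formula without continuity correction gives 141 per arm (stated: 140). Power at 140 per arm is 80.0%. For SBP, 5 mm Hg with SD 15 at 140 per arm gives 79.6% (stated: 80%). The planning figures reproduce, and the issue lies only in the missing-data rule.

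**Inputs.** From the document: attainment of 5% and 15%; SD 15 mm Hg; loss levels of 20% (the allowance first proposed) and 3% (the recent coronary trial); a total of 340, or 170 per arm. Assumed: the split of loss between arms, loss of 5% or 10% in one arm, attainment of 30%, and an SBP fall of 8 mm Hg. Loss is taken as unrelated to outcome within arm.

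**Formula.** A lost patient who was not at goal at baseline is scored a failure. With true attainment p and loss d (C control, I intervention), the difference under carry-forward is

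p_I(1 − d_I) − p_C(1 − d_C).

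It exceeds the true difference when p_C·d_C > p_I·d_I. Mean changes follow the same form.

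**No true effect, 20% control and 5% intervention loss:**

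| True attainment, both arms | False difference | Type I error, 170 per arm (normal approximation) |
|---|---|---|
| 5% | 5 × (0.95 − 0.80) = 0.75 points | 5.2% + 1.1% = 6.3% |
| 15% | 15 × 0.15 = 2.25 points | 8.9% + 0.5% = 9.4% |
| 30% | 30 × 0.15 = 4.5 points | 15.4% + 0.2% = 15.6% |

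The first term in the last column is a false finding for the intervention, against 2.5% nominal. With 20% versus 3% loss, simulated chi-square tests gave 6.5%, 10.8% and 18.8%. With equal loss the error stays near 5%.

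**SBP, no true effect, both arms falling 8 mm Hg, 20% control and 10% intervention loss:** 8 × 0.90 − 8 × 0.80 = 0.8 mm Hg in favour of the intervention.

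**Planned effect, 5% versus 15%.** The difference is inflated only if d_C/d_I > 15/5 = 3. At 20% versus 5%: 15 × 0.95 − 5 × 0.80 = 10.25 points instead of 10. At 3% in both arms: 10 × 0.97 = 9.7 points, and 5 mm Hg becomes 4.85.

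**Heavier intervention loss.** Falls of 13 and 8 mm Hg (true difference 5) with 20% intervention and 10% control loss give 13 × 0.80 − 8 × 0.90 = 3.2 mm Hg. Here the rule is conservative.

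**Patients scored at target without measurement.** On the separate BP-target outcome, suppose 30% to 60% have SBP at or below 140 at entry (assumption). At 20% loss of 170, 34 patients are lost per arm and 34 × 0.30 to 34 × 0.60, about 10 to 20, are counted as successes. At 3% loss it is about 1.5 to 3. The LDL-target outcome works the same way. On the composite this needs one component to be missing with a baseline value at goal while the other is measured at goal, for example entry on SBP with LDL 1.8, six-month SBP 130 and no six-month lipid test.

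**Spread.** Zero changes alone reduce the SD to 15 × √0.80 = 13.4 at 20% loss and 15 × √0.97 = 14.8 at 3%. A shift in mean between measured and filled-in patients gives some back: with an 8 mm Hg fall and 20% loss, √(0.80 × 225 + 0.80 × 0.20 × 64) = 13.8.

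**The case against.** The strongest reply is that the stated check would expose the bias. Using "using only those cases with complete follow-up data for each analysis" replaces the no-change assumption with another: that loss is unrelated to outcome within arm. The examples above assume exactly that kind of loss, so the complete-case result would return the truth: 0 instead of 0.8 mm Hg, 0 instead of 4.5 points, 5 instead of 3.2 mm Hg. This stands. A reader might infer that the check leaves the carry-forward assumption untested; it does not. What it leaves untested is loss that depends on outcome, and carry-forward does not cover that reliably either.

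A reader might also infer that the primary result is likely to be biased by nearly half of the 10-point target. The document does not support that. The 4.5 points need 30% attainment in both arms, against a plan of no more than 5% in controls and 15% with the intervention. Nor does any passage show that controls will be lost more often: they receive monthly nurse visits, the same educational material and the same number of BP readings. The protocol will also examine losses in the first 140 patients randomized, though it does not say by arm.

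Nor should one infer that patients lost entirely are generally counted as composite successes. If above goal on either component at baseline, they are failures. The exception is a patient whose baseline values already meet the endpoint, such as one admitted on the cholesterol ratio alone. That sits badly with "because the proportion at baseline will be zero by definition" but is mainly an eligibility question.

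Finally, not using the monthly SBP readings in the outcome is no error. They come from visits with the study pharmacist or nurse, whereas outcomes are to be collected by blinded, uninvolved staff. Their use as auxiliary variables is a gain in information, not a correction.

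**Conclusion.** The point holds in limited form. The claim of conservatism is wrong as a general property of the between-arm comparison: it is assured only with equal loss or heavier loss in the intervention arm. Under no true effect, heavier control loss yields a false benefit of 0.75 to 4.5 points across 5% to 30% attainment (20% versus 5% loss), or 0.8 mm Hg in the SBP example. At the planned rates, inflation needs a loss ratio above three and is then small. Near 3% loss in both arms the matter is negligible. All sizes rest on an assumed split of loss that the document does not give.

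Counting unmeasured patients as successes is secondary for the composite but applies directly to the BP-target and LDL-target outcomes. The 'on-treatment' label is wrong whatever the loss, because the analysis selects on availability of data, not on treatment received.

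**What to change.** 1. Delete 'conservatively' from the description of carry-forward.
2. Make multiple imputation by arm the primary missing-data method, using baseline SBP and LDL, clinic, and the interim SBP readings as auxiliary variables. Derive the composite and the target outcomes after imputation. Study laboratory samples are scheduled only at baseline, six and 12 months, so imputed LDL will lean mostly on the baseline value.
3. Keep carry-forward as a sensitivity analysis. Add one that scores the composite as not attained whenever either component is unmeasured.
4. Add a tipping-point analysis that varies the assumption about missing patients separately by arm, since neither stated analysis tests outcome-related loss.
5. Rename the 'on-treatment' analysis 'complete-case'.

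The cost is a little more analysis work. No new data, visits or patients are needed.

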### Data management

All data will be collected using standardized data sheets and data collation, entry, quality assurance, and analysis will be carried out by the EPICORE Centre.

### Ethical considerations

Each patient will be given written information about the study and written informed consent will be obtained prior to study entry. The study protocol was approved by the Health Research Ethics Board, University of Alberta (study ID Pro00001556). The funding for the study is from two peer-reviewed grants. The funding sources (the Alberta Heritage Foundation for Medical Research and the Heart and Stroke Foundation of Canada) had no role in the design of the study and will have no role in the conduct, analysis, interpretation, or reporting of the study, nor access to the data.

## Discussion

We report the protocol for a randomized, controlled trial that aims to determine the effect of a pharmacist case manager to improve control of BP and serum lipids in patients with recent ischemic stroke/TIA. There is a large and universally reported care gap in the prevention of vascular disease--even in SPC attendees--and limited data on interventions proven to improve outcomes in patients with stroke or TIA. Studies in other chronic disorders (*e.g*., coronary disease, heart failure, and diabetes mellitus) offer hope that multifaceted interventions employing pharmacist case managers may improve prescribing/dosing of medications and adherence to medications, resulting in improved risk factor profiles and clinical outcomes. However, it is important to develop and prospectively investigate the role of a pharmacist case management program in concert with current standard of care (*i.e*., SPCs) for survivors of stroke/TIA. Because disease management programs do not always work [36,62,63], and the benefits (if present) are often condition-specific, such programs must be tested in controlled trials, rather than just assuming they are beneficial. Although ultimately the multifaceted program we are proposing will be judged by its impact on clinical events, this study has been designed to test the impact of our program on important processes of care (medication management and adherence) as well as intermediate outcomes (such as BP and cholesterol levels) that are well-validated as predictors of subsequent stroke and cardiovascular events.
